### Recruitment, screening and run-in period

Patients will be recruited from the memory clinic of 7 centers above. During the first week, each patient will perform MMSE and HAMD as screen. Then eligible patients will enter a run-in period of 2 weeks, during which they will receive blood tests, electrocardiogram, cranial MRI and a basic computer operation test. The blood tests contain complete blood count, liver and kidney function test, syphilis, folic acid level, vitamin B12 level, thyroid function and ApoE genotype. The purpose of the run-in period is to collect basic clinical data, rule out other causes of cognitive decline and evaluate participants’ compliance. Then all the eligible patients will be registered before baseline assessment.

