### Sample size and statistical analysis

Sample size was estimated based on conversion rate from MCI to AD in the SAS study [28]. In the SAS sample, it was 6.0 per 100 person-years. In the three-year follow-up, the overall probability of conversion event would be 17%. We use hazard ratio (HR) to represent the converting difference of the training group per unit time as the control group. HR represents instantaneous risk over the all period, and is clinically significant due to its indication risks that happen before the endpoint. A power calculation was performed with the online freeware program by “time-to-event” method [29] (http://powerandsamplesize.com).

Due to HR as an almost unprecedented outcome in such sort of trial, we cautiously set 50% reduction in the rate of conversion as estimated effect. With 80–90% statistical power and 12% as the overall probability of conversion within the study period, 544–728 patients in total are considered the minimal number necessary to estimate the hazard ratio. Considering 10% dropout, we plan to enroll approximately 600–800 patients, with 300–400 patients in each group.

As an exploring study, we used per-protocol set instead of intention-to-treat (ITT) analysis as primary endpoint analysis in order to strictly estimate the effect of training. If participants were indicated cholinesterase inhibitors or memantine, or they could not insist on training, they would be excluded from per-protocol sets. ITT approach will also be done to avoid the effects of crossover and dropout. The results of these two analysis will be carefully interpreted.

The randomization is stratified by age and education years according to the Ruijin center using SAS statistical software (SAS Institute Inc., Cary, NC, USA) by a statistician ([name]) with no access to information on the patients or physicians. Patients will be randomized in a ratio of 1:1 to receive the training or only follow-up. In the randomization process, the randomized code is generated and assigned to physicians in a sealed envelope by the statistician. Afterwards, the sealed randomization codes are sent out to each center. The odd number means the training group, while the even number means the control group. If the patient cannot be trained because of difficulty in operating computer or cellphone, the patient will be managed as off-trial.

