Continuous variables (scores of each cognitive assessment) will undergo mixed model analysis in the two groups for the secondary outcomes. At the same time, the effect of ApoE genotype on primary outcome will be observed through analysis of subgroups divided by ApoE genotype in both groups. With regard to MRI, VBM measures and BOLD signal will be used to find out structural and functional changes related with cognitive performance changes.

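### The only ApoE method named for the primary outcome is separate genotype subgroups, which do not estimate whether the training effect differs by genotype

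*Protocol article*

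**What the plan says.** The end of Sample size and statistical analysis in the protocol article states that "the effect of ApoE genotype on primary outcome will be observed through analysis of subgroups divided by ApoE genotype in both groups". Nothing else is said about how ApoE enters the analysis. The same paragraph names a model type for the continuous secondary outcomes (a mixed model), but none for the ApoE question.

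Genotype is determined from blood drawn in the run-in, in a panel that includes "syphilis, folic acid level, vitamin B12 level, thyroid function and ApoE genotype" (Recruitment, screening and run-in period). It is therefore known before randomisation. The stratification factors are age and education, not ApoE (Baseline assessment and randomization).

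The size of the trial follows from three statements in Sample size and statistical analysis. The effect assumption reads "we cautiously set 50% reduction in the rate of conversion as estimated effect". Power and event probability are given there as "With 80–90% statistical power and 12% as the overall probability of conversion within the study period", and the size that results is worded as "544–728 patients in total are considered the minimal number necessary to estimate the hazard ratio". Enrolment is then set with "Considering 10% dropout, we plan to enroll approximately 600–800 patients, with 300–400 patients in each group". That section also describes the trial as exploratory, makes the per-protocol set primary, and adds an ITT analysis.

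**The concern.** The sentence can be read in two ways. It may ask whether training works differently by genotype, or how ApoE relates to conversion within each arm. On either reading, separate estimates in separate groups do not address whether the effects differ. That needs a contrast between the groups with its own standard error.

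If only separate results are available, the natural shortcut is to note which subgroup reaches significance. With few events per subgroup, significance in one and not in the other is a common chance result even when the true effects are equal. The stake is a report that training helps one genotype and not the other when the data do not show it.

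**Working it through.** **Inputs.** HR 0.5, 80–90% power, 12% overall conversion and 544–728 patients are from Sample size and statistical analysis, which also gives the allocation: "Patients will be randomized in a ratio of 1:1 to receive the training or only follow-up". Alpha is not stated. I assume two-sided 0.05 because it reproduces the article's figure; one-sided 0.05 gives 433–600. The number of genotype subgroups and their share of events are not stated. I assume two subgroups, with 30–50% of events in the smaller.

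**Step 1: reproduce the plan's figure.** Schoenfeld events for 1:1 allocation: E = (z₁₋α/₂ + z_power)² / (0.25 × (ln HR)²).
- 80% power: (1.960 + 0.842)² / (0.25 × 0.4805) = 65.3 events; 65.3 / 0.12 ≈ 544.5.
- 90% power: (1.960 + 1.282)² / (0.25 × 0.4805) = 87.5 events; 87.5 / 0.12 ≈ 729.

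These agree with 544–728. Conversely, 544 × 0.12 = 65.3 and 728 × 0.12 = 87.4, so the plan implies about 65–87 events. If none of the 600–800 enrolled dropped out, it would be 600 × 0.12 = 72 to 800 × 0.12 = 96.

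**Step 2: power within a subgroup.** With e events, power = Φ(|ln HR| × √e / 2 − 1.96). At a common HR of 0.5:
- 65 events split 30:70 (19.5 and 45.5): 33% and 65%. Split 50:50 (32.5 each): 51% each.
- 87 events split 30:70 (26.1 and 60.9): 43% and 77%. Split 50:50 (43.5 each): 63% each.

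**Step 3: chance that exactly one subgroup is significant although the true HR is the same in both.** P = p₁(1 − p₂) + p₂(1 − p₁). For 65 events split 30:70: 0.334 × 0.353 + 0.647 × 0.666 = 0.549. The ranges below cover a 30–50% share in the smaller subgroup.

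| Common true HR | 65 events | 87 events |
|---|---|---|
| 0.5 (planned) | 50–55% | 47–54% |
| 0.6 | 43–44% | 48–51% |
| 0.7 | 29% | 34–35% |
| 1.0 | 9.5% | 9.5% |

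A simulation at HR 0.5 gave 50.0–54.9% with 65 events and 46.7–54.2% with 87.

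**Step 4: reading the subgroup HRs without p-values.** The log ratio of the two HRs has SE = √(4/E₁ + 4/E₂). This is 0.54 for 19.5 and 45.5 events, and 0.43 for 43.5 and 43.5. By chance alone the two HRs then differ by a factor above 1.5 in 34–45% of trials, and above 2 in 11–20%.

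**Step 5: what an interaction test does.** At two-sided 0.05 its false-positive rate is 5% (simulated 4.95–5.03%). Its power for a twofold ratio of HRs is Φ(ln 2 / SE − 1.96), which is 25–29% with 65 events and 32–37% with 87. For 80% power the true ratio of HRs would have to be about 0.22–0.25 (65 events) or 0.27–0.30 (87 events).

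**The case against.** The best defence is that the sentence is brief, not wrong. It promises only to observe the effect of ApoE. It does not mention effect modification, within-subgroup p-values or a decision rule. It may mean a prognostic question, and an interaction term may be in an analysis plan that is not at hand. The trial is called exploratory, and ApoE is absent from the study aims and the outcome measures. The near-even rate of discordance also needs a true HR near 0.5, and the proposed test has little power.

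Most of this stands and limits the point. A reader might infer that the trial will declare a genotype difference in half of cases. The documents do not support that: no comparison of significance is stated, and the rate falls to 9.5% if training has no effect. A reader might also infer that a false genotype finding would undermine a stated aim. That is not supported either: the secondary aim on who should receive training concerns patients at the MCI stage as a whole, not selection by genotype.

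Two parts of the defence do not stand. First, the article does not leave the method open. It names one for the primary outcome, and an analysis plan faithful to that sentence would run separate subgroups. The absence of an interaction test alone would be no finding; a named method that does not address differential effect is. Second, the prognostic reading does not rescue it. Comparing arm-specific ApoE effects has the same defect, and for prognosis alone splitting by arm wastes events.

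**Conclusion.** The point holds as a low-cost improvement, not as an error that invalidates the plan. The stated ApoE analysis does not estimate a difference in training effect. The discordance rates apply only if results are compared by significance. They rest on two-sided alpha of 0.05, two independent subgroups, a 30–50% share of events in the smaller one, and the planned event count. The per-protocol primary set may hold fewer events, and more than two genotype classes would lower power in each class further.

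**What to change.** Replace the ApoE sentence with one Cox model containing arm, ApoE ε4 carrier status (carrier or non-carrier) and their interaction. Run it in the randomised (ITT) set, and also in the per-protocol set if wanted. The same model serves both readings of the current sentence.

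Report the interaction estimate (ratio of HRs) with its CI as the basis for any statement on differential effect. Show the subgroup HRs with CIs descriptively only. Label the analysis exploratory and disclose the power of about 25–37% for a twofold ratio of HRs, stating that a non-significant interaction is not evidence of equal effects.

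The cost is analysis wording only. Genotype is already collected in the run-in, so no extra data, patients or visits are needed.

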## Discussion

The SIMPLE trial is leaded by Ruijin Steering Committee ([name], [name], [name]), which is assisted by an independent data safety and monitoring board from Public Health College of Shanghai Jiaotong University School of Medicine (leaded by [name]). The Board includes epidemiologists and statisticians, who are not otherwise participating in the trial. The Steering Committee members and principal investigators of each center ([name] in Shanghai Renji Hospital, [name] in Shanghai General Hospital, [name] and [name] in Shanghai Mental Health Center, [name] in Suzhou municipal hospital, Anhui Province, [name] in Zhoushan Hospital, Zhejiang Province, [name] in Xiangya Hospital, Hu’nan Province) are in charge of the ethics and patient safety. They will have a face-to-face or online meeting every month to monitor the status and progress of the trial. The diagnosis of AD will be reviewed by independent experts in each center and steering committee. The sponsor of the SIMPLE trial is the Clinical Research Center, Shanghai Jiao Tong University School of Medicine. The sponsor has no influence on the study design, data collection, data analysis, and final drafting of the manuscript.

The primary object of this multicenter randomized clinical trial is to explore the effect of multi-model online cognitive intervention for MCI patients. Seven centers are enrolled in the trial and the first patient will be recruited into the study in April 2017. The results are expected for publications in 2022.

## Abbreviations

ACFAS: the American Cognitive Function and Aging Study
ACTIVE: The Advanced Cognitive Training for Independent and Vital Elderly
AD: Alzheimer’s disease
ADAS-Cog: Alzheimer’s Disease Assessment Scale-Cognitive subscale
ADCS-ADL: Alzheimer’s Disease Cooperative Study-Activities of Daily Living
AVLT: Auditory Verbal Learning Test
BOLD: Blood oxygen level dependent
CFT: Complex Figure Test
ChEIs: cholinesterase inhibitors
DSM: Diagnostic and Statistical Manual of Mental Disorders
fALFF: Fractional amplitude of low frequency fluctuation
FDA: Food and Drug Administration
HAMD: Hamilton Depression Scale
HR: Hazard ratio
ITT: intention-to-treat
MCI: mild cognitive impairment due to AD
MMSE: Mini-Mental State Examination
NIA-AA: National Institute on Aging Alzheimer’s Association
Reho: Regional homogeneity
SCWT: Stroop Color-World Test
STT: Shape Trail Test
T2WI: T2 weighted imaging
VBM: Voxel based morphometry
